It is expected that convicted ISAC and ICCSEM under CS, who take part in the web-based intervention, show significantly stronger reduction in self-reported dynamic risk factors inter-, and post-treatment controlling for baseline values as well as less officially recorded re-offenses in a 5-years follow-up, compared to an online-based placebo condition. It is further expected that each individual module of the web-based intervention will have positive effects on its targeted risk factors. The web-based intervention comprises six modules (see Figure 1). For the motivation module it is expected that the motivation to take part in the intervention and the motivation to change the own behavior increases. For the supervision module, it is expected that negative social influences and resistance to rules and supervision decrease while interest in emotionally intimate relationships with adults increase. For the emotion management module, it is assumed that impulsivity as well as dysfunctional coping strategies will decrease. The problem solving module is expected to increase the ability to solve problems. For the offense-supportive attitudes module, it is expected that the agreement with cognitive distortions will decrease. Lastly, it is hypothesized that after the sexuality module, the emotional congruence with children, sexual preoccupation and sexual fantasies with children will decrease. Finally, it is hypothesized that there is a positive net economic benefit. It is expected that the gained tangible benefits (e.g., savings in victim- and offender-related costs) and intangible benefits (e.g., health consequences of pain and suffering and possible loss of life) outweigh the costs of delivering the web-based intervention of @myTabu.

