## 2. Method and Analysis

### 2.1. Design

Up to now, one of the major criticism in RCTs with convicted ISAC and ICCSEM under CS is that mostly the control group was not treated in any way (6). Thus, the clinical trial is designed as an add-on placebo controlled randomized trial with two parallel conditions: (1) web-based intervention (experimental intervention) and (2) web-based placebo condition (control intervention). The placebo condition controls for attention and expectation effects as well as possible effects of contact with the coach. It comprises the same amount of modules with a comparable time effort as the experimental intervention. The topics covered are unrelated to risk factors. Both conditions will be provided as an add-on to the CS as Usual (CSaU). CSaU comprises all orders of the court and treatment as usual [e.g., f2f contacts with supervision officers (SOs), therapeutic treatment ordered by court, medical treatment].

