#### 2.5.2. Secondary Outcome Measures

Pre-post difference scores of psychometric questionnaires in the experimental condition compared to the placebo condition are defined as the secondary outcomes. The questionnaires are assessed before and after each corresponding intervention module. This approach allows evaluating each web-based intervention module individually with regard to its targeted risk factors. Supplementary Table 1 gives an overview over all questionnaires and the respective assessment time-points.

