### 2.11. Statistical Analysis

All patients who discontinue from the study are identified and the extent of their participation in the study is reported. If discontinuation is due to clear evidence for recidivism or concrete preparation for or intention to recidivism (assessed by responsible SO or guiding therapist) the subject receives the maximal value for self-reported dynamic risk factors for the remaining measurements (assuming the worst case of a failed treatment). In all other cases of drop-out, the reason is recorded. The efficacy of the web-based intervention based on the first primary outcome measure (IoD) will be analyzed by means of Gaussian linear model for repeated measures (MMRM) with treatment group, time (six time-points; after each web-based intervention module (see Supplementary Table 1); treatment-by-time interaction, and the randomization strata as factors (offense type, type of CS, external treatment in addition to CSaU), and baseline measurements (at clearing up) of the outcome as co-variate. The error terms are assumed to follow a multivariate normal distribution with unstructured co-variance. Least squares mean changes from baseline are reported for the treatment groups with 95% confidence interval (CI) as well as the difference between the least squares treatment group means with 95% CI and *p*-value testing the null hypothesis of no treatment effect. The analysis is performed on the Intention-To-Treat (ITT) population comprising all patients who have completed at least one module. The second primary outcome measure (officially recorded re-offenses) will be analyzed by means of Cox proportional hazard model with treatment group, number of completed modules and the randomization strata (offense type, type of CS, external treatment in addition to CSaU, risk to re-offend at baseline). The effect of each module will additionally be analyzed using the Wilcoxon signed rank test for paired data comparing the pre- and post-module scores, adjusting the *p*-values using the Bonferroni-Holm's method to control the family-wise error rate. Economic analyses will be based on analytic modeling techniques. Data will be derived from the clinical trial (e.g., recidivism rates based on dynamic risk factors), the literature (e.g., tangible benefits), and experimental procedures (e.g., contingent valuation/revealed preference approaches to assess intangible benefits). Results of the analysis will be presented in terms of net benefit (NB) estimates and a benefit-cost ratios. The NB will be calculated as NB = tangible benefits + intangible benefits-intervention costs. The intervention will be considered cost-beneficial relative to the control condition if the NB is positive and the benefit-cost ratio exceeds 1.00 following standard economic decision rules. Since many cost parameters associated with ISAC and ICCSEM occur after the trial period, the cost-benefit of the intervention will be modeled for a 5-years period. Sensitivity analyses will be conducted to examine how the NB will be influenced by variations in model parameters.

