### 3.1. Limitations

CS of ISAC and ICCSEM in Germany does not include a psycho-therapeutic or medical treatment by default. However, depending on the case and availability of therapists, the court orders an instruction to take part in an external treatment program. Therefore, it is possible that included participants will get additional f2f treatment. This could lead to a potential ceiling effect. Hence, within the clinical trial external treatments are assessed and included in statistical analyses. Since taking part in the study is based on informed consent (and can not be ordered by court until the effectiveness of the web-based intervention has been shown) a volunteer effect can arise. In order to control for a potential volunteer effect, eligible participants who do not want to take part in the study, are asked for informed consent to assess some information consistent with the strata (e.g., prior offenses, modified Static-99 or Static-99) and allowance to assess officially registered re-offenses in the 5-years follow up. Another possible limitation may be the control condition. To control for specific treatment effects, under placebo condition only content is provided which to our knowledge is not able to reduce risk factors. Further, solely online exercises which try to not trigger any internal processes are provided. However, it can not be ruled out that there are (non-specific therapeutic) effects on dynamic risk factors and re-offenses. There is an ongoing discussion which control condition is best for psycho-therapeutic RCTs [for an overview see e.g., (129, 130)]. Due to the fact that mostly psycho-therapeutic placebo conditions can not control for non-specific therapeutic factors and that most psycho-therapeutic treatments contain many components (like the @myTabu web-based intervention) (131), call psycho-therapeutic placebo type controls “pseudoplacebos.” Following this definition, the placebo condition in this study also has to be seen as a pseudoplacebo condition. With regard to self-guided tasks and psycho-educational content provided within both conditions, it is not possible to ensure that participants are not only clicking through the content. This fact is considered by assessing the duration a participant spends on one lesson (each session is subdivided into lessons) which may allow to draw conclusions from the attention allocation to this lesson. However, this measurement controls only for the time spent on a specific lesson not on the engagement during this time. For coach-guided tasks, it is ensured by the coach that the participant is not only clicking through the content.

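### The only stated test of module effects is a paired pre-post signed-rank test that makes no comparison with placebo, although the secondary outcomes are defined as experimental versus placebo

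*Protocol article*

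**What the plan says.** Section 2.5.2 of the Protocol article sets the outcome as a contrast between arms: "Pre-post difference scores of psychometric questionnaires in the experimental condition compared to the placebo condition are defined as the secondary outcomes". The questionnaires are given before and after the corresponding module, and the stated purpose is module-level evaluation: "This approach allows evaluating each web-based intervention module individually with regard to its targeted risk factors".

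Section 2.11 gives module effects one sentence. Each module's effect is, in addition, to be "analyzed using the Wilcoxon signed rank test for paired data comparing the pre- and post-module scores", with p-values adjusted "using the Bonferroni-Holm's method to control the family-wise error rate". The family of tests is not listed. The other two analyses in that section belong to the primary outcomes: a repeated-measures model (MMRM) for the Index of Desistance (IoD) and a Cox model for officially recorded re-offenses. No between-arm analysis of the module questionnaires appears.

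Section 2.1 explains why there is a placebo arm: "The placebo condition controls for attention and expectation effects as well as possible effects of contact with the coach". Section 3.1 adds that, under placebo, "it can not be ruled out that there are (non-specific therapeutic) effects on dynamic risk factors and re-offenses".

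**The concern.** A signed-rank test on pre and post scores tests whether scores moved. It has no arm term, so it cannot test whether they moved more than under placebo, which is the outcome defined in 2.5.2. Time under supervision, external therapy, repeated testing and attention from the coach can act in both arms. Any change they produce could be read as the effect of the module that happened to be running.

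Evaluating each module is a stated aim (1.3), and these questionnaires are the scale-level evidence for it. A claim that a given module works would then rest on an uncontrolled before-after comparison inside a placebo-controlled trial.

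**Working it through.** **1. The texts side by side.** 2.5.2: change in the experimental arm compared with change in the placebo arm. 2.11: post compared with pre, within person. 2.11 does not say whether the paired test is run in the experimental arm, in each arm or in both pooled. None of the three contrasts the arms: two separate within-arm tests give two p-values but no test of their difference, and pooling removes the distinction altogether.

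**2. The plan's own power figure (2.10).** 214 completers per arm, d = 0.27, α = 5%, stated power 80%. SE of the standardised difference = √(2/214) = 0.0967, and 0.27/0.0967 = 2.793. Two-sided power = Φ(2.793 − 1.960) = 0.798. The stated figure is reproduced, and it is power for a between-arm contrast.

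**3. How often the paired test rejects when the module does nothing specific.** Assume the same mean improvement in both arms. The shift δ (in SD of the score) and the pre-post correlation ρ are assumptions; the document gives neither. With n = 214 in one arm:

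- SD of change = √(2(1 − ρ))
- z = δ / SD of change × √(214 × 0.955), where 0.955 is the efficiency of the signed-rank test relative to the t-test under normality; √(214 × 0.955) = 14.30
- rejection probability at 5% ≈ Φ(z − 1.960)

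| δ | ρ | SD of change | z | Rejects at 5% |
|---|---|---|---|---|
| 0.1 | 0.6 | 0.894 | 1.60 | 36% |
| 0.1 | 0.7 | 0.775 | 1.85 | 45% |
| 0.1 | 0.8 | 0.632 | 2.26 | 62% |
| 0.2 | 0.6 | 0.894 | 3.20 | 89% |
| 0.2 | 0.7 | 0.775 | 3.69 | 96% |
| 0.2 | 0.8 | 0.632 | 4.52 | 99% |

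**4. Check by simulation.** 4,000 trials, 214 per arm, normal change scores, same mean change in both arms. Here the shift is in SD of the *change* score, so the rows do not map one to one onto step 3.

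| Shared change | Signed-rank, experimental arm, 5% | Same, at 0.05/6 | Signed-rank, pooled, 5% | Between-arm rank-sum on change, 5% |
|---|---|---|---|---|
| 0 | 5.0% | 0.9% | 5.2% | 5.4% |
| 0.1 | 28% | 10% | 51% | 4.6% |
| 0.2 | 81% | 56% | 98% | 4.4% |
| 0.3 | 99% | 95% | 100% | 4.9% |

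The between-arm test stays near 5% throughout. The paired test does so only when there is no shared change.

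**5. Holm.** The adjustment controls the family-wise error for nulls of no change over time. It does not turn them into nulls of no difference from placebo. In step 3 with δ = 0.2, the strictest step for 16 tests (0.05/16) still rejects in 60% to 94% of cases across ρ = 0.6 to 0.8.

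**6. What the right contrast can detect.** The family size is assumed: 6 (one test per module) or 16 (one per instrument listed in 2.5.2). d is in SD of the analysed change, with 214 per arm.

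| Tests | α at strictest step | Power for d = 0.27 | d for 80% power |
|---|---|---|---|
| 1 | 0.05 | 79.8% | 0.271 |
| 6 | 0.0083 | 56.1% | 0.336 |
| 16 | 0.0031 | 43.6% | 0.367 |

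**The case against.** The best defence is that this is one sentence in a condensed article, that the test is announced as additional, and that 2.5.2 already fixes the between-arm contrast, whose model may stand in an unseen analysis plan. This does not remove the mismatch. The article does name a test for module effects, and the test does not match its own definition. In context the word most naturally means in addition to the two primary analyses, since no other module analysis is stated.

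Other parts of the defence stand and limit the point:

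- A reader might infer that the placebo arm is discarded. It is not. The MMRM for the IoD has treatment group and treatment-by-time terms at six time-points, one after each module, and one IoD component, the Checklist of Treatment Effectiveness, covers the constructs targeted by the modules. That comparison is cumulative and composite, so it does not replace a scale-level module test.
- A reader might infer that modules will be declared effective simply because everyone changes over a month. Nothing in the document establishes such a change. Placebo exercises are designed to have no lasting effect (2.4), and 3.1 says only that non-specific effects cannot be excluded. With no shared change the paired test holds its level.
- Regression to the mean is a weak explanation here, because eligibility (2.2.1, 2.2.2) does not select on any of these scales.
- A between-arm test is not a clean isolation of a module either. Modules run in a fixed order (2.3), so from module 2 on the pre-module score is itself post-randomisation and may already differ by arm.

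**Conclusion.** The point holds, within limits. The stated module test cannot answer the question that 2.5.2 poses, in whichever arm or arms it is run. This rests on the text alone and needs no assumption.

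The size does depend on assumptions: about 36% to 99% rejection at 5% with no module-specific effect, for an assumed shared shift of 0.1 to 0.2 SD, an assumed correlation of 0.6 to 0.8, and 214 completers in one arm. These figures show what could happen; they do not predict what will.

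The defect is confined to the scale-level evaluation of modules. Neither primary outcome analysis nor the sample size depends on this test. It should be fixed, but it does not undermine the trial's main comparison.

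**What to change.** Reconcile 2.11 with 2.5.2 before unblinding:

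1. For each scale, make the module analysis a between-arm comparison of the pre-to-post-module change. One option is a linear model of change with arm, the randomisation strata and, where the scale was measured then, the clearing-up baseline. Another is a stratified rank-sum test on change. The clearing-up baseline is preferable to the pre-module score as covariate, because from module 2 on the latter is measured after randomisation.
2. Declare the family of scales over which Holm is applied.
3. Keep signed-rank results as descriptive, reported by arm.
4. State that, with modules in fixed order, each contrast isolates a module only conditionally on the earlier ones.
5. State the power at the strictest Holm step: for d = 0.27 and 214 per arm, about 56% with 6 tests or 44% with 16.

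The cost is wording plus that lower power. Section 2.6 says the placebo procedure differs only in online content, so no new data collection should be needed. The assessment schedule in Supplementary Table 1, not available here, should be checked to confirm this.

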
### 2.12. Stopping Rules

The individual subject is excluded from the clinical trial if the responsible SO or the online coach reports clear evidence for sexual recidivism or concrete preparations for any sexual recidivism. The clinical trial is stopped if an interim analysis at the mid-point of the project (12 months after first patient in; tested on subjects having completed at least two modules of the web-based intervention) demonstrates: (a) a significantly higher risk to re-offend (based on main outcome and number of reported significant events in the experimental condition compared to the placebo condition); (b) a significantly higher proportion of reported significant events (see a) in the experimental condition than in the placebo condition; (c) a significantly increased proportion of high-risk subjects (defined in terms of the main outcome) compared to the proportion at baseline.

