### 2.6. Procedure

The clinical trial starts on January 01, 2021 and ends on December 31, 2022. All potential participants are screened by their SO based on inclusion criteria and the SO hands out written information on the trial. If the potential participant is generally interested in participating, an individual meeting with an independent research assistant will take place at the supervision office. During this meeting, the research assistant provides detailed information about the goals and procedure of the trial, data security and advantages or disadvantages of taking part in the trial. If the potential participant is further interested to take part, he or she will receive an information letter, the informed consent, an intervention agreement, and a letter releasing the SO from the confidentiality obligation. In the intervention agreement, the participant agrees not to commit offenses during the participation and is informed that any violation will lead to exclusion. Furthermore, the research assistant performs the pre-intervention assessments (see Supplementary Table 1). If a potential participant does not want to take part in the trial, he or she will be asked for informed consent in filling out one questionnaire (QNP) and to allow to fill out the SSQ-CF checklist by the research assistant as well as the SSQ-SO by the SO. Further, the potential participant is asked for allowance to assess his or her officially registered re-offenses in a 5-years follow up in order to be able to control for a potential volunteer-effect. After obtaining the written informed consent, the intervention agreement, and the release from confidentiality, the participant is randomly allocated to the experimental or the control condition. The username as well as the initial password is delivered by post to the SO, who will give it to the participant. After the first log-in, the participant has to change the initial password due to security reasons. After changing the initial password, the participant has to go through an introduction, which explains the usage of the intervention website, before he or she can start with the first online module. The procedure for the placebo condition is the same as for the experimental condition, only the provided online contents differ. In both the placebo and the intervention condition, the provided content is divided into six online modules. Each module is further divided into four sessions. Each session has a duration of about 60 min and the participant is advised to finish one session per week. Consequently, the intervention as well as placebo consists of 24 sessions which can be completed in 24 weeks. The participant will be reminded by in-app messages or by the SO if he or she is late in finishing the next session. During both online conditions, data of primary outcome (IoD) is assessed at 7 measurement time-points. Except questionnaires which are filled out at clearing up all questionnaires are provided online within the web-based app. This ensures that the questionnaires are filled in at the predefined measurement time-points. Five years after the last patient out, re-offenses are assessed by officially documented re-offenses (see Supplementary Table 1 for an overview on measurement time-points).

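### The interim comparisons of significant events count only participants who finished two modules, so anyone removed earlier for recidivism is left out

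*Protocol article*

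**What the plan says.** Section 2.12 (Stopping Rules) of the protocol article contains two rules that interact.

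- Individual removal: "The individual subject is excluded from the clinical trial if the responsible SO or the online coach reports clear evidence for sexual recidivism". Preparations for such an offence have the same result. No minimum time in the trial applies.
- Trial-level stop: "an interim analysis at the mid-point of the project (12 months after first patient in", with the analysis set described as "tested on subjects having completed at least two modules of the web-based intervention". This restriction comes before the three criteria and so governs all of them.

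Criterion (a) concerns a higher risk to re-offend, judged on the main outcome and on the number of reported significant events, experimental against placebo. Criterion (b) concerns a higher proportion of reported significant events "in the experimental condition than in the placebo condition". Criterion (c) concerns "a significantly increased proportion of high-risk subjects (defined in terms of the main outcome) compared to the proportion at baseline".

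Section 2.11 assigns the worst score on self-reported risk factors, for all remaining measurements, to participants who discontinue because of recidivism or its preparation. Nothing there or in section 2.12 says that this brings an early removal into the interim set.

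**The concern.** Completing two modules happens after randomisation, and whether it happens depends on the harm that the interim is meant to detect. A participant removed in module 1 or 2 because of recidivism will never complete two modules, so that event never reaches the formal comparison, however late the interim is held. Early drop-outs are lost in the same way, together with any event reported for them.

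If the intervention raised risk soon after it began, the removals would fall mainly in the experimental arm. The two-module set would then consist of those who came through the early period without removal, and the arms could look alike. These are the only trial-level between-arm harm criteria that the article describes, so a weakened test matters both for participants and for the public.

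**Working it through.** **1. Time to enter the interim set.** Figure 1 gives 4 weeks per module, so 2 × 4 = 8 weeks at the protocol's pace. The one-week lock between sessions rules out a much faster pace: the eighth session cannot open until 7 weeks after the first was finished, even without delays.

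**2. Does the restriction cover both arms?** The words could be read as the experimental arm only. However, the Figure 1 legend uses the term for both conditions, and (a) and (b) need both arms. I take it to cover both.

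**3. The plan's own figures.** The article gives no operating figure for the interim rule. Its sample size reproduces: n = 2(1.96 + 0.842)²/0.27² = 216 per arm, and 214 per arm gives 79.8% power; 582 × (1 − 0.264) = 428. No sample-size figure is in dispute.

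**4. How many are outside the set at 12 months.** Assume uniform recruitment of 582 over R months.

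- Randomised by month 12: 582 × 12/R, which is 388 (R = 18) or 291 (R = 24).
- With 8 weeks elapsed: 582 × (12 − 8/4.345)/R, which is 328 or 246.
- Assumed loss before the end of module 2: from 8.8% (the planned 26.4% spread evenly over six modules, two of them counted) to 26.4% (all of it early, a ceiling).
- In the set: 300 to 242 (R = 18) or 225 to 181 (R = 24).
- Outside the set: 88 to 146, or 66 to 110.

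Of those outside, 388 − 328 = 60 or 291 − 246 = 45 are only recent enrolees. The number removed early for recidivism cannot be derived from the article.

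**5. Effect on criterion (b), as an illustration.** Assumed true event rates are 6% on placebo and 12% on the experimental arm. The 6% borrows the recidivism level cited in section 1.1 and is not an estimate of events in this trial. Assume also that every event before the end of module 2 leads to removal. With true rate p and early share s, the rate seen in the two-module set is p(1 − s)/(1 − ps). For half of placebo and three quarters of experimental events early:

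- placebo: 0.06 × 0.5/(1 − 0.03) = 0.03/0.97 = 3.1%
- experimental: 0.12 × 0.25/(1 − 0.09) = 0.03/0.91 = 3.3%

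Power for a two-sided 5% test of two proportions is Φ[(Δ − 1.96 × SE₀)/SE₁], with SE₀ pooled and SE₁ unpooled. The number per arm is held fixed so that only the effect of the rates shows: 150 is half of 300, and 194 is half of 388.

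| Early share, placebo / experimental | Rates seen | Power, 150 per arm | Power, 194 per arm |
|---|---|---|---|
| none (all events count) | 6.0% / 12.0% | 44% | 54% |
| 1/3 / 1/3 | 4.1% / 8.3% | 33% | 41% |
| 1/2 / 1/2 | 3.1% / 6.4% | 27% | 33% |
| 2/3 / 2/3 | 2.1% / 4.3% | 20% | 24% |
| 1/2 / 3/4 | 3.1% / 3.3% | 3% | 3% |

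With equal early shares the ratio of the rates stays near 2 and the loss is one of events and power. With more early events in the experimental arm the contrast itself disappears.

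**The case against.** **The trial watches for early harm in other ways.** Individual removal acts at once. The Mood and Risk Questionnaire (section 2.5.3.5), with six items on thoughts and behaviours linked to re-offending, is given before and after each session. Supervision officers report repeatedly on conduct (SSQ-rSO, section 2.2.3.3), and there is an independent data safety monitoring board (section 2.8). All of this stands. A reader might infer that the trial is blind to early harm, and the article does not support that. The gap is in the formal between-arm tests at 12 months.

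**A minimum exposure has a rationale.** The IoD is scored after modules, and the first module addresses motivation before risk factors are targeted. This stands for the IoD-based components. It gives no reason to require module completion before an event is counted.

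**Most of those outside the set may carry no harm information.** This also stands: 45 to 60 of them are merely recent, and the upper end of the range places the whole planned drop-out before the end of module 2.

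**Criterion (c).** A reader might infer that (c) is wrong because it has no placebo comparator, and that a drift common to both arms would stop the trial falsely. The documents do not support calling this an error. Criteria (a) and (b) already compare with placebo, and (c) can be read as a deliberate absolute safeguard against deterioration in both arms. The drift is also conjecture. Section 2.6 says "Except questionnaires which are filled out at clearing up all questionnaires are provided online within the web-based app", which shows that clearing-up questionnaires are collected outside the app but not that scores would rise afterwards. Any false-stop probability would rest on an assumed drift and an assumed baseline share at high risk.

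**Conclusion.** The point holds for the event components of criteria (a) and (b). It follows from the wording of section 2.12 alone: removal before the end of module 2 and membership of the interim set exclude each other, so these comparisons are conditioned on no early removal. Participants removed after module 2 stay in the set.

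The size cannot be fixed from the article, because neither the rate nor the timing of significant events is given. In the illustration, power falls from 44% to between 20% and 33% when early events are equally common in both arms as a share of all events, and to 3% when they cluster in the experimental arm. If few events occurred in the first 8 weeks, the loss would be small.

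The population is stated explicitly, so this is a badly fixed rule and not a detail left to a fuller plan. The individual removal rule is not in question, and neither is the place of criterion (c).

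**What to change.** In section 2.12, and in the monitoring board's charter if it repeats the wording:

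- For the event components of (a) and (b), analyse all randomised participants by allocated arm. Count reported significant events and removals for recidivism or its preparation from randomisation, including those before the end of module 2.
- For the IoD-based components, the two-module set may stay. State that the worst-value rule of section 2.11 applies at the interim to participants removed for recidivism.
- Leave criterion (c) in place.

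The cost is a change of wording. Supervision officers and coaches already report these events, and allocation is known for every randomised participant, so no new data collection is needed. Recent enrolees add little information on events, but including them restores the randomised comparison.
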